#### Methods in analysis to handle protocol non-adherence and any statistical methods to handle missing data {20c}

Careful trial planning and execution will minimize the occurrence of missing data as far as possible. In cases where data is missing, treating physicians will be contacted to complete the data from patients’ records. If none of the valid reasons to ignore missing data as cited in Jakobsen’s practical guide [33] is fulfilled, multiple imputation by chained equations will be performed using the R package “mice” [34]. A sensitivity analysis will be performed on the dataset of patients treated without major protocol deviations, such as delay or noncompliance with the medication plan. Any changes or deviations from the original statistical plan will be reported to the ethics committee.

#### Plans to give access to the full protocol, participant-level data, and statistical code {31c}

We plan to publish this protocol, meaning it will be accessible to the public. The complete statistical methods and results will also be published as soon as data collection and analysis are completed. Upon request, competent authorities (CA) will have full access to anonymized patient data and complete statistical code.

### Oversight and monitoring

#### Composition of the coordinating center and trial steering committee {5d}

[name] at the medical university clinic of the cantonal hospital Baselland leads this study, which is the coordinating center. The multidisciplinary research team includes medical doctors, a clinical pharmacologist, study nurses, statisticians, and public health scientists. Furthermore, the study team is supported by the clinical trial unit from the clinical research department at the university hospital of Basel. A trial steering committee is not planned.

#### Composition of the data monitoring committee, its role, and reporting structure {21a}

All study data and documents shall be accessible to monitors, and questions will be answered during monitoring. The sponsor will perform the site initiation visits and the close-out visit. Scheduled monitoring time points are after the inclusion of the first ten patients and after the last visit of the last patient.

#### Adverse event reporting and harms {22}

##### Reporting of SAEs

An adverse event (AE) is defined as any untoward medical occurrence in a patient, or a clinical investigation participant administered a pharmaceutical product, which does not necessarily have a causal relationship with the study procedure. An AE can be any unfavorable and unintended sign (including an abnormal laboratory finding), symptom, or disease, whether or not related to the medicinal (investigational) product. A serious adverse event (SAE) is classified as any untoward medical occurrence that results in death, is life-threatening, requires in-patient hospitalization or prolongs existing hospitalization, results in persistent or significant disability/incapacity, or is a congenital anomaly/congenital disability.

In addition, critical medical events that may not be immediately life-threatening, result in death, or require hospitalization but may jeopardize the patient or require intervention to prevent one of the other outcomes listed above should also usually be considered serious.

All SAEs must be reported immediately and within a maximum of 24 h to the sponsor-investigator of the study. The sponsor-investigator will re-evaluate the SAE and return the form to the site. SAEs resulting in death are reported to the ethics committee via BASEC within 7 days.

All involved ethics committees receive SAEs resulting in death in Switzerland via sponsor-investigator via BASEC within 7 days.

##### Reporting of suspected unexpected serious adverse reactions (SUSARs)

A SUSAR needs to be reported to the ethics committee (local event via the local investigator) via BASEC and to Swissmedic for category B and C studies (via sponsor-investigator) within 7 days if the event is fatal, or within 15 days (all other events).

The sponsor-investigator must inform all investigators participating in the clinical study of the occurrence of a SUSAR. According to the exact timelines, all in the trial involved ethics committees will be informed about SUSARs in Switzerland via the sponsor-investigator via BASEC.

##### Reporting of safety signals

All suspected new risks and relevant new aspects of known adverse reactions that require safety-related measures, i.e., so-called safety signals, must be reported to the sponsor-investigator within 24 h. The sponsor-investigator must report the safety signals within 7 days to the ethics committee (local event via the local investigator) via BASEC and to Swissmedic in case of a category B or C study.

The sponsor-investigator must immediately inform all participating investigators about all safety signals. The other ethics committees involved in the trial will be informed about safety signals in Switzerland via the sponsor-investigator.

##### Reporting and handling of pregnancies

Pregnant participants must immediately be withdrawn from the clinical study. Any pregnancy occurring during the treatment phase of the study and within 30 days after discontinuation of study medication will be reported to the sponsor-investigator within 24 h. The administration of vitamin D3 is not contraindicated in pregnancy, but hypercalcemia caused by long-term overdose can lead to various negative outcomes for the child. Furthermore, since the evidence for the effect of high-dose vitamin D in patients with COVID-19 remains uncertain, it was decided to exclude pregnant women. Pregnant women with a known vitamin D deficiency should be supplemented according to prescribing information or according to the recommendations of the treating gynecologist.

##### Periodic reporting of safety

An annual safety report (ASR) is submitted once a year to the local ethics committee by the local investigator and to Swissmedic in case of a category B study, as this study is categorized, via the sponsor-investigator.

#### Frequency and plans for auditing trial conduct {23}

Independently from investigators, regulatory authorities can audit this trial. Study documentation and data are accessible to auditors/inspectors, and questions are answered during inspections. All involved parties must keep the participant data strictly confidential.

#### Plans for communicating important protocol amendments to relevant parties (e.g., trial participants, ethical committees) {25}

Substantial amendments are only implemented after approval of the local ethics committee (LEC) and Swissmedic, respectively.

Under emergency circumstances, deviations from the protocol to protect human subjects’ rights, safety, and well-being may proceed without prior approval of the sponsor and the LEC/CA. Such deviations shall be documented and reported to the sponsor and the LEC/CA as soon as possible. All non-substantial amendments are communicated to the CA as soon as possible.

#### Dissemination plans {31a}

We aim to publish the results of this study in a peer-reviewed journal. There is no intention to use professional writers. This trial is registered at www.clinicaltrials.gov and kofam.ch and is therefore accessible to the public.

## Discussion

The primary aim of this study is to determine whether a high dose of vitamin D improves the course of COVID-19 or not. Two issues might affect the ability to recruit patients for this trial: first levels of vitamin D are the highest by the end of summer [35], which could lead to problems in recruiting. After the full ethics approval and the approval from Swissmedic, the recruitment period is expected to start at end of 2020 or early 2021. Shorter days and less exposure to sunlight most certainly lead to a decreasing serum concentration of vitamin D. Therefore, we anticipate that we will not have recruiting problems due to high vitamin D levels.

Secondly, travel regulation and other policies can change day by day and are carefully monitored by the Swiss government, which leads to a more unpredictable situation for this and other studies investigating COVID-19.

While the number of patients hospitalized with COVID-19 declined between April and August, numbers have started to rise again. Latest studies have shown a link between international and domestic air travel and the number of COVID-19 cases, so unless air travel is restricted again, we can expect an increasing number of cases [36, 37]. The same can be applied for lockdown policies and other public health measures, leading to decreasing cases [38, 39] and subsequent rebounds after gradually releasing the measures.

There are minimal risks in the participation in this study. Almost no side effects are reported when using a high vitamin D dosage, but it has a potential short and may also long-term benefit [23, 24, 40]. Some recent findings indicate an association between vitamin D deficiency and disease severity [23, 41, 42]. However, there is a lack of consensus on the dosage of vitamin D supplementation [40]. With this trial, we hope to make a valuable contribution in clarifying the role of vitamin D in COVID-19 and its effect on short-term outcomes. The crucial point is that vitamin D supplementation is a simple, safe, and inexpensive possibility to correct vitamin D deficiency, with potential benefits to patients with COVID-19 [43]. On a larger scale, the benefit that effective treatment of vitamin D deficiency in patients with COVID-19 could have on the overall costs of the health care system must also be considered. The authors hope to make a valuable contribution to future treatment guidelines for patients with COVID-19.

## Trial status

This study was submitted to the local ethics committee the first time at the end of May 2020. After the feedback, we revised the study protocol to change the design from an open label to randomized controlled double-blind. Other changes were made in the protocol (version 3.1., 26.07.2021), which was approved by the regional ethics committee without further obligations in August 2021. This trial was also submitted to Swissmedic and got the approval in October 2020. We submitted this protocol to *Trials* first in November 2020, and revisions came back in September 2021. Neither the submitting authors nor the Editor of the Journal can explain what happened in the meantime. We could include the last patient for this trial in mid of September 2021. The follow-up (28 days and 3 months) quality of life will be terminated by mid-November 2021.

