### Outcomes {12}

As the primary outcome, we fixed the length of the hospital stay. Therefore, the measurement will be the overall duration of the hospitalization from enrolment until discharge from hospital care. As defined, to measure the secondary objectives, we will assess if there are any differences between the TAU + VitD and the TAU + placebo group in terms of the variables described in the table below.

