**Table Tabb:** 

ICU stay	Yes/no
	If yes, length of the ICU stays (admission to discharge)
	Requirement for mechanical ventilation
Overall mortality	
Vitamin D serum concentration	% of patients with 25-(OH)D > 50 nmol/L at day 7
	25-(OH)D
Laboratory parameters	Calcium
	Phosphorus
	Parathyroid hormone (PTH)
Sepsis	% of patients who develop a sepsis
Complications	Complications during the hospitalization due to COVID-19
Vital signs	Blood pressure (BP)
	Heart rate (HR)
	Respiratory rate (RR)
	Blood oxygen saturation
	Need of oxygen and how much
Quality of life (SF-12 Questionnaire)	At baseline, 28 days, and 3 months after inclusion

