### Participant timeline {13}

### Sample size {14}

To calculate the sample size, we looked at an interventional study of vitamin D, which examined the length of hospital stay as an outcome and what is known about the median length of hospital stay in patients hospitalized with COVID-19. A randomized, double-blind, placebo-controlled trial examined the effects of adjunctive vitamin D in adults hospitalized with community-acquired pneumonia (CAP) on time to recovery [28]. The primary outcome was the complete resolution of chest radiograph infiltrates at 6 weeks post-study treatment. Secondary outcomes included length of hospital stay, intensive care admission, and return to regular activity. At the same time, adjunctive vitamin D did not affect the primary outcome (*OR* 0.78, 95% *CI* 0.31 to 1.86, *p* = 0.548). There was evidence it increased the complete resolution of pneumonia in participants with baseline vitamin D levels < 25 nmol/L (*OR* 17.0, 95% *CI* 1.40–549.45, *p* = 0.043). Although not significant, the results indicated that patients in the intervention group had shorter length of hospital stay (mean = 3.8, *SD* = ± 3.1, *n* = 60) when compared with patients in the placebo group (mean = 4.8, *SD* = ± 6.5, *n* = 57), which indicates a small effect size (Cohen’s *d*) of 0.1980. The study indicated a 20% reduction in length of hospital stay.

Considering the above results in the light of COVID-19, more extended hospital stays in COVID-19 patients are expected. In smaller observational studies describing the clinical course of hospitalized COVID-19 patients in China, a median hospital stay of 12 days (*IQR* 9–15) (*n* = 137) [1] or of 10 days (*IQR*, 7.0–14.0) among those discharged alive (*n* = 47) [29] were observed. Guan et al. presented the clinical characteristics of 1099 patients with laboratory-confirmed COVID-19, and the median length of hospital stay was reported to be 12 days (*IQR* = 10–14) [30], which we will take as a basis for our sample size calculation.

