Sample size calculation was performed using the function “power.t.test” from the R package “stats” with the following parameters [31]: alpha = 0.05, power = 0.80, sigma = 2.96, delta (difference in the primary outcome between intervention and control group) = 2, and alternative hypothesis = two-sided, which resulted in a minimum of 35 patients per group, therefore a total of 70 patients. With a conservatively estimated 10% dropout rate, including the loss to follow-up, and a block size randomization of four, we decided to include 80 patients.

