### Data collection and management

#### Plans for assessment and collection of outcomes {18a}

All outcomes are assessed by treating physicians or nurses until discharge or fatality. The CRF is provided either electronically (Web-based) or in paper form, in which case it will be sent by mail or fax to the coordinating study center, where data will be entered into the Web-based database.

The primary outcome is the length of hospital stay. The exact length will be calculated automatically by the electronic database into which only the date of the admission, the date of inclusion in the study, and the date of discharge must be entered. With this method, copying or calculation errors can be minimized. Patients are screened daily and therefore we will have only a small delay of approximately 1 day from hospital admission until inclusion to the study.

Secondary outcomes are the following:

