### Statistical methods

#### Statistical methods for primary and secondary outcomes {20a}

A statistical analysis plan documented detailed methodology for summaries and statistical analyses of the data collected in this trial. The statistical analysis plan is finalized analysis [31]. We will summarize our results using descriptive statistics.

The primary analysis comparing the mean length of hospital stay between the two groups will be performed on the dataset of all randomized patients for whom the outcome measure is available. A two-sided independent Student’s *t*-test will be used following log-normal transformation as Feng et al. [32] suggested. The time to discharge will be assessed up to 3 months, with failure to reach discharge or die before that day considered as right censored at 3 months. Patients who are admitted to ICU or change wards within the hospital can continue the study and their data can be analyzed as planned, since the intervention can be continued, and daily visit data are available within the electronic patient documentation system. For patients who are transferred to another hospital, the primary endpoint will be taken from the respective discharge letter, which is by standard sent from the following hospital to the referring hospital. If this data is not available, the patient will be considered as right censored at the date of transfer.

In the secondary outcome analyses, mean levels of calcium, phosphorus, 25-hydroxyvitamin D, 1,25-dihydroxy vitamin D, and PTH will be compared using two-sided independent Student’s *t*-tests. To compare the proportion of patients who died, were admitted to ICU, developed sepsis, and as the proportion of patients with 25-hydroxyvitamin D ≥ 30 ng/mL at discharge between the two groups, either the χ ^2^ test or the Fisher exact probability test will be used. The Fisher exact probability test is an excellent non-parametric technique for comparing proportions when the two independent samples are small.

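### The stated end of quality-of-life follow-up (mid-November 2021) falls about one month before the last 3-month SF-12 is due (mid-December 2021)

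*Protocol article*

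**What the plan says.** Two consecutive sentences in the Trial status section fix the calendar. On the end of recruitment: "We could include the last patient for this trial in mid of September 2021". On the end of follow-up: "The follow-up (28 days and 3 months) quality of life will be terminated by mid-November 2021".

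The outcome table under Outcomes {12} sets the SF-12 schedule: "At baseline, 28 days, and 3 months after inclusion". The table under Plans for assessment and collection of outcomes {18a} repeats it. The clock therefore starts at each patient's inclusion.

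The length-of-stay endpoint also has a 3-month horizon, given in Statistical methods {20a}: "The time to discharge will be assessed up to 3 months". No calendar closing date is attached to that endpoint.

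**The concern.** A 3-month assessment counted from inclusion cannot be finished for a patient who joined only two months before follow-up closes. The sentence giving the closing date names the 3-month assessment explicitly, so it cannot be read as referring to the 28-day questionnaire alone.

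If the dates are followed as written, the 3-month SF-12 of late-included patients is either never collected or collected early and filed under the wrong time point. In the first case the calendar builds in missing data, although the section on missing data {20c} promises to keep missing data to a minimum. In the second, the 3-month results mix assessments made at about two months with assessments made at three. Either could be avoided: the article speaks of the end of follow-up as still to come.

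**Working it through.** **Inputs**

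- Last inclusion: mid-September 2021 (Trial status). Taken as 15 September, range 10 to 20 September.
- End of quality-of-life follow-up: mid-November 2021 (Trial status). Taken as 15 November, range 10 to 20 November.
- SF-12 due at 28 days and 3 months after inclusion (tables under {12} and {18a}).

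The article gives no day of the month. Reading 'mid' as the 10th to the 20th is an assumption, and the range shows what it can change.

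**Step 1: time available to the last patient.** End date minus last inclusion.

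- Central: 15 November − 15 September = 61 days.
- Shortest: 10 November − 20 September = 51 days.
- Longest: 20 November − 10 September = 71 days.

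**Step 2: date on which the last patient's SF-12 is due.**

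- 28 days: 15 September + 28 days = 13 October (range 8 to 18 October). This is before mid-November, so it fits.
- 3 months: 15 September + 3 months = 15 December, 91 days after inclusion (range 10 to 20 December). This is after mid-November, so it does not fit.

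**Step 3: shortfall.** Due date minus end date.

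- Central: 15 December − 15 November = 30 days (also 91 − 61 = 30).
- Smallest: 10 December − 20 November = 20 days.
- Largest: 20 December − 10 November = 40 days.

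No reading of 'mid' closes the gap.

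**Step 4: who is affected.** A 3-month SF-12 can be done by the stated end only if inclusion date + 3 months is no later than the end date. That means inclusion no later than 15 November − 3 months = 15 August 2021 (range 10 to 20 August). Patients included between then and mid-September cannot have the assessment on time. Accrual by month is not given, so they cannot be counted.

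**Step 5: does the same gap reach the primary endpoint?** The closing date is attached to quality of life only. Length of stay is defined as "the overall duration of the hospitalization from enrolment until discharge from hospital care", and section {18a} says: "All outcomes are assessed by treating physicians or nurses until discharge or fatality". Neither sets a calendar cut-off. For scale, suppose discharge data had also stopped in mid-November. Only a late-included patient still in hospital after about 61 days could be cut short. The planning basis is a median stay of 12 days (IQR 10–14). With a log-normal stay, the log-SD implied by that IQR is (ln 14 − ln 10) / 1.349 = 0.25, and P(stay > 61 days) = 1 − Φ[(ln 61 − ln 12) / 0.25], which is practically zero. With larger assumed log-SDs of 0.5, 0.7 and 0.9 the probability is 0.06%, 1.0% and 3.5%.

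**The case against.** The strongest reply is that this is one forward-looking sentence in a narrative section, that both tables say 3 months, and that one of the two months may simply be misprinted. That is possible, and the documents do not show whether a date is wrong or which one. But the two dates and the schedule cannot all be true, and no visit window in the text would let an SF-12 about 30 days early count as the 3-month one. The participant timeline figure could not be read for this check.

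It can also be said that a calendar cut-off acts alike on both arms, since allocation is 1:1 in blocks of four within centre. This stands. The problem is completeness and labelling of one secondary outcome, with some loss of precision, and no bias in the treatment comparison has been shown.

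Three stronger readings are tempting and are not supported:

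- **The primary endpoint is truncated because it too runs to 3 months.** The mid-November date applies to quality of life only, and nothing in the article ends collection of discharge or death data then.
- **The lost questionnaires use up the 10% dropout allowance.** That allowance sizes the length-of-stay comparison. A patient without a 3-month SF-12 still contributes a length of stay, so power is unchanged.
- **About 8 to 10 patients are affected.** This follows from 80 patients spread evenly over 8 to 10 months (80/10 = 8; 80/8 = 10). The article does not give accrual by month or the number actually enrolled. Its Discussion also expects vitamin D levels to be highest by the end of summer, which makes even accrual doubtful for exactly this window.

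**Conclusion.** The point holds for the 3-month SF-12. By the article's own dates, follow-up closes about 30 days (20 to 40) before the last 3-month questionnaire is due, and patients included after about mid-August 2021 cannot complete it in time. At least the last patient is affected; the total is unknown. The only assumption is how 'mid' is read, and the conclusion does not depend on it.

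The effect is confined to the 3-month time point of one secondary outcome. The 28-day SF-12, the primary endpoint and its censoring rule, the sample size and the power are untouched. It is worth acting on because, if the dates are real, following them loses or mistimes data that could have been collected.

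**What to change.** Reconcile the two dates in Trial status with the SF-12 schedule in the tables under {12} and {18a}.

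- If both dates are real, keep 3-month SF-12 collection open until 3 months after the last inclusion, about mid-December 2021. The cost is about one more month of questionnaire contacts.
- If either date is a slip, correct it. The cost is a change of wording.
- If collection did close in mid-November, report how many late-included patients lack a 3-month SF-12, by arm. Do not count values taken at about two months as 3-month values.

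Nothing in the primary analysis or the sample size section needs to change on this account.
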